### Participant selection

Participants will be recruited from memory clinics, old age mental health services and GP practices, and will have been diagnosed with early-stage Alzheimer’s disease (AD), vascular dementia, or mixed AD and vascular dementia. For each participant, a carer (a family member or close friend who is either co-resident or in regular contact) will also be involved.

Inclusion criteria:

1. The participant must have been assigned an ICD-10 diagnosis of Alzheimer’s disease (AD), vascular dementia, or mixed AD and vascular dementia. AD accounts for 62% of dementia diagnoses, and vascular dementia for 17%, with mixed AD and vascular dementia accounting for a further 10%
[2]. These categories together capture 89% of those diagnosed with dementia. There is no reason to assume that people with rarer subtypes of dementia, including dementia with Lewy bodies (4%), fronto-temporal dementia (2%) and Parkinson’s dementia (2%), could not benefit from CR, but these forms of dementia have specific features that would require a distinct approach. For this reason, and because numbers are likely to be too small to allow for subgroup analysis, we are not proposing to include these groups in the current trial.

2. The participant must be in the early stages of dementia, as indicated by an MMSE score of 18 or above. This is to ensure that participants recruited to the trial have a level of cognitive functioning that is sufficient to allow them to complete the selected outcome measures without undue difficulty for the duration of their participation in the study. Use of a cutoff point, while inevitably somewhat arbitrary, provides protection for people who may be overly burdened by the assessments. The selected cutoff of a score of 18 on the MMSE is frequently used in research studies and worked well in the pilot trial. We have not placed any upper limit on the MMSE score, since it can be expected that a small proportion of people meeting diagnostic criteria for dementia will have high MMSE scores
[57].

3. If taking acetylcholinesterase inhibitors, the participant must have been receiving a stable dose for 1 month prior to trial entry, and there should be no intention to change the dose over the period of participation in the study unless clinically indicated. This is to ensure that intervention effects are not confounded by changes in medication status.

4. The participant must have a carer who is willing to participate. While having a carer is not an essential prerequisite for receiving a CR intervention, it is important for the purposes of research to obtain an informant perspective on the effects of the intervention, and in this trial carers will be asked to provide an independent rating of goal performance. It is also important to determine the effects of the intervention on carer well-being; positive effects on the carer are likely to bring added benefits in the longer term for the person with dementia.

5. The participant must be able to give informed consent. People in the early stages of dementia are normally expected to have capacity to consent to participation. When recruiting participants, the research team will use a checklist to ensure that all relevant information is considered and that the participant is able to give informed consent. While CR principles may be applied at any stage of dementia, the intervention to be tested here involves engaging the person with dementia in a collaborative process of identifying and addressing personally meaningful goals, and therefore the participant needs to be able to understand this and to make a positive choice to take part.

Exclusion criteria:

1. Participants will be excluded if they have a prior history of stroke, brain injury or other significant neurological condition. Such conditions would be expected to affect cognitive, behavioural and emotional functioning, and people who have one of these conditions prior to developing dementia would have additional rehabilitation needs. While such individuals might benefit from CR, their inclusion would represent a potential confounding factor.

2. Participants will be excluded if they are unable to speak English. This criterion is applied for practical reasons, because the standardised outcome measures we plan to use are only available in English. No official data are available to indicate what proportion of the UK population cannot speak English; while it is estimated that about 3% of the population use a language other than English at home, with over 100 different languages represented (source: The National Centre for Languages), many of the individuals concerned also speak English. The time and costs involved in translating standardised measures and providing interpreters for assessment and therapy sessions would be substantial. However, we predict that very few individuals would be excluded from participation because of inability to communicate in English.

### Ethical considerations

The study has been reviewed by the North Wales Research Ethics Committee–West, which issued a favourable opinion on 25 June 2012 (Reference 12/WA/0185) and has been approved by the Bangor University School of Psychology Research Ethics Committee.

Based on previous findings, participants randomised to receive CR may be expected to derive some benefits in terms of managing everyday activities and general well-being. Their caregivers may also be expected to show reduced stress and improved well-being. Availability of evidence from a definitive trial may be expected to have a positive influence on the future provision of interventions to support people with early-stage dementia and their carers. Previous findings also suggest that participants randomised to TAU are expected to show little or no change; thus, they will not be harmed by this allocation. As the trial will provide the first evidence from a large-scale trial regarding the benefits of CR, it cannot at this stage be considered unethical to withhold this treatment from the control group, and the control group will still have access to the care typically provided by memory clinics and GPs, and to voluntary sector services.

There are no known risks or side effects associated with CR. It is possible that some participants may find it challenging to confront their difficulties, but the therapist will provide support as they engage in this process, and the intervention protocol incorporates attention to managing emotional reactions. Neither the feasibility studies nor the pilot trial have suggested that this represents a significant risk to participants. The research team will be trained to be alert to any concerns about participants’ well-being. If there are serious concerns about a participant, these will be referred, wherever possible with the permission of the individual concerned and the carer, to the clinician responsible for the participant’s care.

Participants with early-stage dementia, and carers, will be fully informed prior to entry into the trial about the intervention and about the current state of knowledge regarding possible benefits and risks, and this information will be updated if additional evidence becomes available during the course of their participation.

Informed consent will be obtained from all participants and carers. People with early-stage dementia are expected to have the capacity to consent to participation. While consent provided at the outset provides an initial mandate for entry to the trial and commencement of trial procedures, consent is an ongoing process, and this is crucial for psychosocial interventions where participants’ active engagement is required. Therefore, research assistants and therapists will be trained to monitor ongoing consent and to respond appropriately to any indication of a possible withdrawal of consent. As participants will be in the early stages of dementia, loss of capacity to consent during the course of participation is expected to be infrequent. However, on entry to the trial participants will be asked whether, should they lose capacity to consent, they are willing to continue to be included in the trial and to have their data used.

Personally identifiable information will be retained only until publication of the trial report unless the participant has consented to retention of details for potential further follow-up, while anonymised data will be retained for 5 years after publication unless a longer period is required by the Research Ethics Committee or other regulatory authorities. Consent forms will be retained for 25 years following trial closure.

The governance and management of the study will be undertaken within the Department of Health Research Governance Framework for Health and Social Care (2nd edition, 2005). This will ensure the highest standards of clinical research, covering scientific quality, ethical standards and all related management issues. The trial will adhere to the Standard Operating Procedures (SOPs) of NWORTH CTU
[58] for all trial and data management, statistical and regulatory matters. This is not a clinical trial of an investigational medical product (CTIMP) and therefore it does not come under the provisions of the Medicines for Human Use (Clinical Trials) Regulations (2004).

All research staff and therapists will undergo training in Good Clinical Practice with regard to the conduct of clinical trials. Trial-specific training requirements will be addressed throughout the study period and regularly reviewed. Orientation and project-specific training will be provided for CLRN, MHRN and NISCHR CRC staff.

### Sample size

Power calculations and attrition rates are based on findings from the pilot trial. We wish to confirm the finding that the primary effectiveness outcome of goal performance was improved in the treatment group
[45]. The difference observed in the pilot was large (standardised effect >1 at post-intervention assessment). However, we also wish to detect any effect sizes in the order of 0.3 for important secondary outcomes, as we judge that this will give confirmation of effects that are large enough to have substantive clinical benefits. For the present study, intervention length has been increased and now includes a maintenance phase in order to further strengthen demonstrable effect sizes in secondary outcomes. We have elected to be conservative in all aspects of our estimate of power, and we have made a larger estimation of potential attrition than the <20% observed in that study, based on the 27% rate observed in the recent REMCARE trial
[59]. To achieve 80% power to detect a medium effect size of 0.3, with alpha 0.05, in primary and secondary outcomes, 175 PwD, with their carers, need to complete the trial in each arm. Adjusting for potential attrition, we aim to randomise 480 PwD, each with a carer. There will be one practitioner involved at each centre, and we will test for differences between sites in the analysis. If there is a change of practitioner at one or more centres during the course of the trial we will also test for practitioner effects.

### Outcome measures

#### (1) Primary outcome measure

##### Bangor Goal-Setting Interview (BGSI)

The BGSI
[52] provides a structured format for the goal-setting process. The interview proceeds in three stages. First, relevant domains of functioning are discussed in turn with a view to eliciting issues that might form the basis for behavioural goal-setting. For each area, the participant rates perceived importance of making changes in this area, and readiness to make changes in this area, on a 1 – 10 scale (where 1 is not at all important/not at all ready and 10 is extremely important/completely ready). Once all areas have been discussed, the second stage involves revisiting each area in turn and negotiating specific behavioural goals that conform to ‘SMART’ principles (specific, measurable, achievable, realistic and time-delineated). Additionally, goal attainment indicators are specified, providing clear descriptors of what would constitute 25%, 50% and 75% goal attainment. In the final stage of the interview, the participant is asked to rate, for each of the goals that have been identified, current performance and satisfaction with performance on a 1 – 10 scale (where 1 is unable to perform/extremely dissatisfied and 10 is able to perform perfectly/extremely satisfied). Mean scores for performance and satisfaction with performance across goals are calculated by dividing in each case the sum of the scores for all goals identified by the number of goals set. For the present study, details of the goals identified in the baseline BGSI assessment will be provided to the therapist for each participant allocated to the CR condition and will form the starting point for the therapist’s intervention. At follow-up assessment, the participant re-rates current performance and satisfaction with performance for each goal so that changes in ratings can be examined. The interviewer elicits information about current performance and uses the previously specified goal attainment indicators to rate the extent of progress towards achieving the goal. There is scope within the interview format for informant ratings to be obtained; in this study, carer ratings of performance and descriptions of goal attainment will be elicited at baseline and follow-up for comparison purposes.

#### (2) Secondary outcome measures for participants with dementia

##### DEMQOL

DEMQOL
[60] has been designed to assess health-related quality of life of people with dementia across the full range of severity and subtypes, and shows high internal consistency (Cronbach’s alpha 0.87) and good test-retest reliability (ICC 0.76) in people with mild to moderate dementia. It consists of a 28-item interviewer-administered questionnaire for the person with dementia and a 31-item interviewer-administered questionnaire on which the caregiver provides proxy ratings. These may be used together or separately. In this study, only self-ratings by the person with dementia will be taken. An algorithm has been developed to generate quality-adjusted life year (QALY) scores from DEMQOL scores for use in economic evaluation
[61].

##### Generalised Self-Efficacy Scale (GSES)

The ten-item Generalised Self-Efficacy Scale (GSES)
[62] was created to assess a general sense of perceived self-efficacy, the potential to influence one’s situation through one’s own actions. Responses are made on a 4-point scale. Responses to all ten items are summed to yield the final composite score with a range from 10 to 40. Cronbach’s alphas range from 0.76 to 0.90
[63].

##### Hospital Anxiety and Depression Scale (HADS)

The HADS
[64] contains 14 items forming two subscales: anxiety and depression. Each item is rated on a 4-point scale, giving maximum scores of 21 for anxiety and for depression. Scores of 11 or more on either subscale are considered to be a significant ‘case’ of psychological morbidity, with scores of 8–10 classified as ‘borderline’ and 0–7 ‘normal’. The HADS has been employed and validated in studies of people with dementia and carers
[65,66].

##### Brief cognitive assessment battery

This will consist of brief tests of memory, attention and executive function, suitable for people with early-stage dementia, each taking less than 5 min to administer: (1) Memory: Rivermead Behavioural Memory Test (RBMT)
[67], story recall subtest. The RBMT is a well-established, ecologically valid test of everyday memory. In the story recall task, the researcher reads out a short story, similar to a brief report of a newsworthy event in a daily newspaper, and the participant is asked for immediate and delayed (after 20 min) recall of the content. Recall is scored following a standard protocol (inter-rater reliability > 0.9) with a maximum possible score of 21 for the immediate and for the delayed component. Four equivalent versions are available to permit reassessment without the risk of practice effects; practice effects are not anticipated with test-retest intervals of 3 and 6 months, but as a precaution a different version will be used at each time point. Raw scores will be used in the analysis as they provide a greater range than the condensed standardised profile score that is used in calculation of the overall RBMT score. (2) Attention: Test of Everyday Attention (TEA)
[68], elevator counting and elevator counting with distraction subtests. The TEA is a well-established, ecologically valid test of everyday attention, with subtests assessing different components of attention. The elevator counting subtest assesses sustained attention. Participants are required to count a short string of monotonous tones and give the total number. Seven strings are presented, and the total score is the number of strings correctly counted. The elevator counting with distraction subtest assesses auditory selective attention. Further strings of tones are presented, this time also including distractor (high-pitched) tones that are not to be counted. The total score is the number of strings correctly counted. Three equivalent versions of each subtest are available to permit reassessment without the risk of practice effects; as above, practice effects are not anticipated but as a precaution a different version will be used at each time-point. (3) Executive function: Letter fluency subtest of the Delis-Kaplan Executive Function System (D-KEFS)
[69]. D-KEFS consists of a set of standardised tests of executive function. The verbal letter fluency task evaluates the executive subdomains of initiation, response generation and inhibition
[70] and draws on semantic memory and language ability. In this task, the participant is asked to list as many words as possible beginning with a specific letter of the alphabet in a 1-min period, excluding proper nouns and repetitions. Three letters, F, A and S, are used. The total number of correct responses to the three letters is used in analysis. This task has been extensively examined in people with early-stage dementia
[71]. Evidence suggests that even in healthy participants there are no practice effects for most components of this task even at test-retest intervals of less than 2 weeks; there are minimal practice effects for the switching component with test-retest intervals of less than 2 weeks, but not with longer intervals.

#### (3) Secondary outcome measures for the carer

##### Relatives’ Stress Scale (RSS)

The RSS
[72] is a 15-item dementia-specific measure of caregiver stress with items rated on a 5-point Likert scale and summed. A higher overall score indicates higher levels of caregiving-specific stress.

##### EuroQOL (EQ5D)

The EQ-5D
[73] is a standardised measure of health status and health outcome, applicable to a wide range of health conditions. In the first section, the respondent is asked to select one of three options for each of five dimensions: mobility, self-care, usual activities, pain/discomfort and anxiety/depression. For each dimension, the three response options are coded on a 3-point scale from 1 (no problem) to 3 (unable to perform/extreme problem). This yields a descriptive profile (e.g. 11232) across the five dimensions. The second part of the measure is a visual analogue scale for self-rating of health-related quality of life (‘your health state today’). This measure is included because the EQ5D score will be used to generate QALY scores using societal weights.

##### WHO Quality of Life – BREF(WHOQOL-BREF)

The WHOQOL-BREF
[74] is a 26-item scale assessing perceived quality of life, giving scores in four domains: environment, social relationships, psychological and physical health.

#### (4) Service utilisation

##### Client Services Receipt Inventory (CSRI)

The CSRI
[75] provides a template that can be adapted to the needs of each specific study. Respondents are asked about their use of health care services for a period preceding baseline assessment and during the study period. The questions cover contact with a range of health and social care professionals, prescription of medications, hospital appointments and stays, participation in local authority funded activities such as day centres, participation in activities run by voluntary organisations and the contribution of informal carers. Questions to examine the nature and extent of any dementia-specific treatment received from the Memory Clinic will be included.

#### (5) Demographic and background information for the person with dementia and carer

Details such as gender, age, relationship between person with dementia and carer and whether they live together, age of onset of dementia, educational level, social class and co-morbidities will be collected. This will allow us to examine effects of demographic and social variables on treatment efficacy.

#### (6) Process measures for the CR group

For the cognitive rehabilitation group, process measures will be taken to provide convergent evidence about change in goal performance. In-session parallel ratings of goal performance by participant, carer and therapist will be made when each goal is introduced and in session 10. A simplified goal attainment scaling procedure
[43] will be applied, as described for the pilot trial; clearly specified behavioural indicators of full and partial goal achievement will be defined when each goal is introduced, and progress according to these criteria will be rated by the therapist following session 10 and again following session 14.

#### (7) Therapist adherence to protocol

Therapist adherence to the treatment protocol will be monitored through therapy logs and structured supervision sessions. Therapists will receive monthly telephone supervision and face-to-face supervision meetings will be held every 3 months. Therapy logs reporting session content (with participant details anonymised) will be submitted to the supervisor for scrutiny prior to supervision sessions.

#### (8) Treatment compliance

Treatment compliance will be indexed by the number of sessions completed for each participant.

### Procedure

Initial identification of participants will be made by National Institute for Health Research (NIHR) Comprehensive Local Research Network (CLRN) and Mental Health Research Network (MHRN) staff in England and National Institute of Social Care and Health Research Clinical Research Collaboration (NISCHR CRC) staff in Wales. Participants will be contacted by or on behalf of the clinician responsible for their care and invited to respond directly to the research team to express an interest in finding out more about the study. Interested participants and carers will then be contacted by telephone by the local research assistant, who will provide additional information and send out written details. This will be followed by a further telephone call; for those interested in finding out more, a meeting will be arranged at which the research assistant will explain the study, answer any questions they may have, re-check eligibility and ensure that the person with dementia has the capacity to consent. Consent from the participant and the carer will be taken at, or following, this visit.

At each centre, once participants have given informed consent, they will be visited by the research assistant who will conduct the baseline assessment. Following this assessment, the research assistant will trigger randomisation. Results of the randomisation will be sent to the therapist, who will telephone the participant and the carer to explain the next steps. Participants allocated to CR will receive 10 weekly visits from the therapist over a 3-month period. The therapist will trigger the post-intervention assessment for all participants. The research assistant will visit each participant to conduct the assessment. Following the post-intervention assessment, participants in the CR group will receive four maintenance sessions with the therapist over a 6-month period. The research assistant will visit all participants 6 months after the post-intervention assessment to carry out the final 6-month follow-up assessment. All primary and secondary outcome measures, and service utilisation measures, will be administered at each assessment point.

After consent and baseline assessment, participants will be individually randomised. Randomisation to GREAT will be achieved by secure web access to the remote randomisation centre, NWORTH CTU, at Bangor University. This system will be set up, maintained and monitored independently of the trial statistician or other trial staff. The randomisation will be performed by dynamic allocation
[76] to protect against subversion while ensuring that the trial maintains good balance to the allocation ratio of 1:1 both within each stratification variable and across the trial. Participants will be stratified by centre, gender, age (under 75 *vs.* 75 and above) and MMSE score (under 24 *vs.* 24 and above). For validation purposes, additional information will be taken including the participant’s trial number, initials, and date of birth, and details of the person requesting the randomisation.

This is a single-blind trial. The researchers taking the measures will be blind to allocation, as will the data analysts. The importance of maintaining blinding will be emphasised in the training for both research assistants and therapists. As the participants are not blind to their treatment, at post-intervention and follow-up assessments participants will be specifically asked not to comment on the nature of their involvement in the study and not to reveal to the researcher whether or not they were visited by the therapist. Following each assessment, the blinded researcher will note to which condition s/he thought the participant had been allocated and how certain s/he was of the allocation. Sensitivity analyses will be performed to determine whether this knowledge affected participant scores. If there is evidence to suggest that consequential bias is present, the analysis will be adjusted to counteract this effect.

Other protection from bias will include the method of allocation to groups. The randomisation will be performed independently of the data analysis team by the CTU using a dynamic, stratified, web-based system designed to protect from bias by the unpredictability of the algorithm and the security of the web-based programme. Blinding will be maintained by automatic generation of randomisation codes and distribution via e-mail directly to the therapists responsible for implementing the treatment. Further bias protection will come from a “treatment as allocated” analysis, which will be the principal analysis performed on both primary and secondary outcomes. Treatment compliance measures will be restricted to inclusion in secondary analyses.

We will collect basic anonymised demographic data and reasons for not progressing to trial participation for all those people identified as warranting screening and invitation to the trial but declining to be screened or to participate. These data will be reported on a CONSORT diagram, together with information on the amount and nature of missing data, to enable readers to assess bias arising from recruitment or acceptability issues within the trial.

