### Statistical analysis

Demographic and baseline data will be fully described and all outcome data will be analysed and reported. Significance will be assumed to be 5% throughout, and 95% confidence intervals will be quoted. All data will be anonymised and coded so that data collection and statistical analysis are blind to treatment allocation. The code will be broken only after the primary analysis has been completed. A fully pre-specified analysis plan will be prepared prior to the data being released to analysts. The analysis will be performed on a “Treatment as Allocated” principle to ensure protection against unintended bias. The data will be fully imputed in line with the pre-defined statistical analysis plan to minimise data loss due to missing values or time points. Sensitivity analyses (best case/worst case) will be performed to assess the influence of differing imputation assumptions. All trial reporting will be CONSORT-compliant
[77].

For each outcome measure, at both post-intervention and follow-up, three analyses will be presented, the first two being unadjusted and adjusted treatment-as-allocated analyses and the third a treatment received analysis:

1. An unadjusted two-sample *t*-test by allocation group.

2. An analysis of covariance with baseline score and stratification variables as the covariates and allocated group as the condition factor. Between-group effect sizes with confidence intervals will be calculated using Cohen’s d. Centre will be added as a fixed factor to test and quantify any site-specific effects, and if the number of practitioners is greater than the number of centres, practitioner will be added as a random factor.

3. A repeat of analysis 2 with treatment compliance factored in.

If CR is shown to be effective, additional forward stepping regression modelling will be undertaken to identify factors important in maximising the observed effects. Factors that will be investigated will include diagnostic category, medication status, educational level, social class, caregiver relationship to the person with dementia (spouse, adult child, other), and whether or not the carer is residing with the person with dementia.

For the cost-effectiveness analysis (CEA), service utilisation and carer input data will be collected using the CSRI. Unit costs will be attached to service use measures (from national reference costs, the PSSRU compendium

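### Adjusting the analysis on evidence from an allocation guess recorded after the outcome cannot separate assessor bias from a real effect, and could remove genuine effect

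*Protocol article*

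**What the plan says.** Protocol article, *Procedure* (blinding paragraph): participants know their treatment and are asked not to reveal it. Then come three linked steps.

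- Record: "Following each assessment, the blinded researcher will note to which condition s/he thought the participant had been allocated", together with the degree of certainty.
- Examine: "Sensitivity analyses will be performed to determine whether this knowledge affected participant scores".
- Act: "If there is evidence to suggest that consequential bias is present, the analysis will be adjusted to counteract this effect".

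*Bangor Goal-Setting Interview (BGSI)* shows what the assessor knows by then. For the primary outcome, "At follow-up assessment, the participant re-rates current performance and satisfaction with performance for each goal so that changes in ratings can be examined". In addition, "The interviewer elicits information about current performance and uses the previously specified goal attainment indicators to rate the extent of progress towards achieving the goal".

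*Procedure* also makes the treatment-as-allocated analysis the principal one for primary and secondary outcomes. *Statistical analysis* lists three analyses for every outcome. The adjusted one is "An analysis of covariance with baseline score and stratification variables as the covariates and allocated group as the condition factor". The guess appears in none of the three.

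**The concern.** The guess is treated as a measure of knowledge that may have affected scores. It is taken after the scores are known to the person guessing, so influence can run either way. *Sample size* reports a pilot effect on goal performance above 1 SD. An assessor who has just heard of marked improvement has reason to guess cognitive rehabilitation (CR) even if scoring was entirely fair.

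Two things are at stake. First, an association of this kind may be read as evidence of bias when there is none. Second, the stated response is to change the analysis. Guess and certainty are the only data the paragraph collects for the purpose, so conditioning on the guess is the natural way to do it. That conditions on a post-outcome variable, and the change would be made after seeing the data. The clause does not say which analysis is altered, which sits badly with a principal analysis fixed as treatment-as-allocated.

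**Working it through.** **The plan's own figures.** *Sample size* gives an effect of 0.3, alpha 0.05 (two-sided assumed), 80% power and 175 completers per arm. The check is 2 × (1.960 + 0.842)² / 0.3² = 174.4, so 175. With 27% attrition, 350 / 0.73 = 479.5, so 480. Both reproduce and are not in dispute. They set the scale below: true effect 0.30 SD and 350 analysed.

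**Assumptions, because the article gives no guess data.** Score = 0.30 × arm + standard normal error, with no assessor bias. The log-odds of guessing CR rise by 0.5, 1 or 2 per SD of score, so the odds multiply by e^0.5 = 1.6, e^1 = 2.7 or e^2 = 7.4. The adjustment is taken to be the guess added as a covariate; the article names no method.

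**Formula.** In least squares, adjusted effect = unadjusted effect - (guess coefficient × between-arm gap in the proportion guessed CR). At 1:1 allocation the gap is 2 × (proportion of correct guesses) - 1.

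| Slope | Correct guesses | Gap | Guess coefficient | Adjusted effect | Power (from 80%) |
|---|---|---|---|---|---|
| 0.5 | 0.517 | 0.034 | 0.473 | 0.30 - 0.016 = 0.28 | 77% |
| 1 | 0.532 | 0.064 | 0.828 | 0.30 - 0.053 = 0.25 | 72% |
| 2 | 0.545 | 0.090 | 1.212 | 0.30 - 0.109 = 0.19 | 60% |

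At a true effect of 1.0 SD, slopes 1 and 2 give 0.83 and 0.64.

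**With disclosure.** Suppose 30% of participants also reveal their arm, so that the guess is correct for them, still with no effect on scoring. A true 0.30 becomes 0.18, 0.08 and -0.05 at slopes 0.5, 1 and 2. A true zero becomes -0.11, -0.19 and -0.28.

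**Would the condition protect?** The article sets no test. If significance of the guess coefficient were used, its z at 350 participants without disclosure is 4.5 or more for slopes of 0.5 and above, with no bias present. In simulated trials it was significant in 99% to 100%. At slope 0.2, z is about 1.9 and the estimate 0.297, so both the false signal and the harm are small there.

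**Cases where adjustment is harmless or right.**
- If the outcome does not influence the guess (slope 0), 0.30 stays 0.30.
- Suppose belief formed before scoring, was correct in 73.1% (gap 0.462) and added 0.2 SD to scores. The unadjusted effect is then 0.30 + 0.2 × 0.462 = 0.39, and adjustment restores 0.30.

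In both the harmful and the helpful case the analyst sees a positive guess coefficient and subtracts coefficient × gap. In one case this removes bias and in the other it removes effect. A guess recorded after the assessment does not show which.

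**The case against.** The strongest reply is that the article never says the guess will be a covariate. Adjustment is conditional on evidence of consequential bias, and the criterion and method can properly be left to the analysis plan that *Statistical analysis* promises before data release. The three listed analyses omit the guess and will be presented regardless. The figures above rest on assumed slopes and an assumed disclosure rate, although participants are asked to stay silent.

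Much of this stands. The missing criterion and method are not a finding, and the sizes are illustrations. What does not fall away is the stated rule. It says the analysis will be adjusted, does not confine that to a sensitivity analysis, and relies on a variable that cannot identify bias. Setting a threshold in a later plan would not cure that.

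Two stronger readings are tempting. A reader might infer that the plan adjusts for the guess outright and so will shrink the effect. The text supports only a conditional adjustment of unnamed form, and that the outcome influences the guess is an inference from the order of events. A reader might also infer that the trigger fires most readily when CR works. The calculation does not support this: for a guess coefficient adjusted for arm, z is about the same at true effects of 0, 0.3 and 1.0.

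**Conclusion.** The concern holds in conditional form. The article commits to altering the analysis on evidence drawn from a belief recorded after the outcome was heard and rated, and such evidence cannot separate detection bias from a real effect that informed the guess. If the adjustment uses the guess as a covariate and there is no assessor bias, a true 0.30 SD would be reported as 0.28 to 0.19 for slopes of 0.5 to 2, or 0.18 to -0.05 with 30% disclosure. The loss is nil at slope 0, and the adjustment is beneficial if prior belief truly inflated scores. It is unclear whether the principal result would change, because the clause does not name its target. That ambiguity should be removed.

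**What to change.** Replace the adjustment clause with two statements: the treatment-as-allocated ANCOVA remains the unmodified principal analysis whatever the guess data show; and any analysis using guesses or disclosure is a labelled, pre-specified sensitivity analysis that does not replace it.

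On the assessment form, record the guess, its certainty and any actual disclosure with its timing before the BGSI re-rating. Log later disclosure separately. Report all of these by arm.

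The cost is a change of wording and one form change. The form change has to be in place before follow-up assessments, since the timing cannot be recovered afterwards. A guess taken before the BGSI misses unblinding during the interview, and the disclosure log covers that only in part. Any analysis that excludes disclosed assessments needs the caveat that it conditions on a post-randomisation event, which may differ between arms.
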